#### 4.6 Multiple comparisons and multiplicity

Each of the primary outcomes will be tested at the 5% significance level. No adjustment to the significance level will be made for secondary or tertiary outcomes, subgroup analyses or sensitivity analyses. The total number of tests will be reported to allow interpretation of the risk of type I error.

#### 4.7. Clustering

Inclusion of infants from multiple (twin or triplet) pregnancies in the analysis is a potential source of clustering. To account for the effect of clustering, generalised estimation equations (GEEs) with interchangeable correlations will be used.

### 9. Power calculation

This study involves the follow-up of a historical clinical trial and the sample size is limited to the number of participants able to be located. For the primary outcome *composite of cardiovascular risk factors*, the sample size of 420 allows for detection of a 15% increase in the proportion with the outcome (relative risk 1.33) with 90% power ( $\beta = 0.10$ ) at a significance level of 5% ( $\alpha = 0.05$ ), assuming a baseline prevalence of 45% in the placebo group. For the primary outcome *Age at first major adverse cardiovascular event*, the sample size of 420 allows for detection of a hazard ratio of at least 0.33 with 90% power ( $\beta = 0.10$ ) at a significance level of 5% ( $\alpha = 0.05$ ), assuming a baseline prevalence of 8% in both the placebo and steroid groups.

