### 13. Statistical Analysis

Statistical analysis will be performed for all primary, secondary and tertiary outcomes. Statistical significance will be tested at the 5% significance level using a two-sided test of significance. Analyses will compare the antenatal corticosteroid (betamethasone) group to the control (cortisone acetate) group.

Analyses for binary outcomes will be performed using log binomial regression analysis, reported as relative risk (RR) with 95% confidence intervals.

For continuous outcomes, analysis will be by general linear modelling after assessing model assumptions, using an identity link function and normal distribution.

For time-to-event analyses, a Cox proportional hazards model will be used, reported as a hazards ratio (HR) with 95% confidence intervals. The assumption of proportionality will be verified and if required time dependent functions modelled. Competing risk models will be used if appropriate.

For the hierarchical win-ratio outcome, analysis will follow a stepwise approach in which the six components of the composite outcomes are assessed sequentially (2). The six steps in the hierarchy will start with time to death after randomisation, followed by time to major adverse cardiovascular event, diagnosis of diabetes mellitus, number of admissions to hospital for respiratory illness, self-reported general health and time spent in hospital per 10 years alive. For each step, participants in the treatment and control group will be compared in all possible pairs to determine “wins”, “losses” and “ties”. Pairwise comparisons with ties or missing data at any step will be assessed at the next sequential step in the hierarchy. The analysis will then determine the ratio of the probability of wins and losses for the treatment. The resulting odds ratio will be reported with 95% confidence intervals (2).

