### **Addendum to statistical analysis plan for Auckland Steroid Trial Follow up**

The following text will replace section 4.7 for the approach to clustering:

Inclusion of infants from multiple (twin or triplet) pregnancies in the analysis is a potential source of clustering, as is women having more than one pregnancy included in the study. To account for the effect of clustering of infants from the same mother, random effects model will be used.

The following bullet point will be added to the first list in section 4.8 for sensitivity analyses:

- Excluding the second child in cases of women having more than one pregnancy within the study.

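### At the plan's own inputs, 420 participants give about 87% power for the primary risk-factor composite, not the stated 90%

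*SAP*

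**What the plan says.** Section 9 of the SAP states that a sample size of 420 permits "detection of a 15% increase in the proportion with the outcome (relative risk 1.33) with 90% power" at a 5% significance level, "assuming a baseline prevalence of 45% in the placebo group". It names no formula, allocation split or allowance for clustering.

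Two other places fix the test. Section 13: "Statistical significance will be tested at the 5% significance level using a two-sided test of significance". The multiplicity paragraph in section 8 (numbered 4.6): "Each of the primary outcomes will be tested at the 5% significance level". The 5% is therefore two-sided and is not divided between the two primary outcomes. Section 13 also says that binary outcomes are analysed by log binomial regression and reported as relative risks.

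The first addendum replaces the clustering paragraph. It names multiple births, and women with more than one pregnancy in the study, as potential sources of clustering, and continues: "To account for the effect of clustering of infants from the same mother, random effects model will be used". Neither the addendum nor section 9 gives an intraclass correlation, a share of clustered participants or a design effect.

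**The concern.** The power sentence gives every input needed to check it except the allocation split, and the standard two-sided calculation on those inputs does not return 90%. It is the stated power of a primary outcome. The study hypothesis (section 2.2) is that antenatal corticosteroids have no long-term adverse impact, so a null result on this composite is likely to be read as reassurance. A reader who weighs that result needs the actual chance of missing an increase of the stated size. The sentence also makes no mention of clustering, although the analysis allows for it.

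**Working it through.** **Inputs.** Total 420 (section 9), taken as 210 per arm (assumption). Placebo proportion p1 = 0.45 (section 9). Relative risk 1.33 = 0.60/0.45, so the 15% is 15 percentage points and p2 = 0.60. Two-sided alpha 0.05 (section 13), z = 1.96, with no split between primary outcomes (section 8). For 90% power, z = 1.2816.

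**Attempt to reproduce the stated 90%, pooled formula.**
- Mean proportion = 0.525; sqrt(2 × 0.525 × 0.475) = 0.7062.
- sqrt(0.45 × 0.55 + 0.60 × 0.40) = sqrt(0.4875) = 0.6982.
- Power = Φ[(0.15 × sqrt(210) − 1.96 × 0.7062)/0.6982] = Φ[(2.1737 − 1.3842)/0.6982] = Φ(1.131) = 87.1%.

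The stated figure is not reproduced.

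**Sample size for 90%.** n per arm = (1.96 × 0.7062 + 1.2816 × 0.6982)² / 0.15² = 2.279² / 0.0225 = 230.8, so 231 per arm and 462 in total. The 420 is 42 short, 9% of 462.

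**Wald test on the log relative risk, the closest to the planned log binomial analysis.**
- SE = sqrt[(0.55/0.45 + 0.40/0.60)/210] = 0.0948.
- ln(0.60/0.45) = 0.2877.
- Power = Φ(0.2877/0.0948 − 1.96) = Φ(1.073) = 85.8%.

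**Other two-sided methods at 210 per arm.**

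| Method | Power |
|---|---|
| Unpooled variance | 87.6% |
| Pooled variance | 87.1% |
| Arcsine | 87.1% |
| Exact enumeration of the chi-square test | 86.6% |
| Wald, log odds ratio | 86.6% |
| Wald, log relative risk | 85.8% |
| Continuity-corrected formula | 84.9% |

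Taking the relative risk as exactly 1.33 (59.85% against 45%), the pooled formula gives 86.4%.

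**Allocation.** A split of 190:230, either way round, gives 86.8%. Equal arms are close to the most favourable case, so the assumption does not create the shortfall.

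**Detectable difference with 420.** Solving the pooled formula for 90% power gives p2 = 0.607: 15.7 points, relative risk 0.607/0.45 = 1.35.

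**Clustering, illustration only.** Participants are analysed by their mother's allocation, so twins share an arm and a positive within-pregnancy correlation reduces the effective number to 210/DE per arm. The design effects (DE) below are assumed; none is in the SAP.

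| Assumed DE | Power (pooled) |
|---|---|
| 1.02 | 86.4% |
| 1.05 | 85.4% |
| 1.10 | 83.8% |

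**The case against.** The strongest reply is that little turns on the difference. Section 9 says that the sample is limited by how many participants can be located, so 420 was not derived from the power target. The gap is 2.9 power points, or 0.7 points of detectable difference, which is small against the uncertainty in the 45%. If the relative risk is held at 4/3, a placebo prevalence of 47% already gives 90.0% at 210 per arm. The second addendum adds gestational diabetes to the composite, which cannot lower its prevalence. All this stands as an argument about size. It does not make the sentence right at the 45% it states. The rescue also depends on which effect is held fixed: with 15 points added to 47% (47% against 62%), the pooled formula gives Φ[(2.1737 − 1.96 × 0.7042)/0.6962] = 87.3%.

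A second reply is that other conventions come closer to 420. A one-sided 5% test needs 376 in total, or 404 with continuity correction (412 if the relative risk is exactly 1.33). A 15-point decrease, 45% to 30%, gives 89.1% with 420. A reader should therefore not infer that no convention comes near the figure. These readings nevertheless conflict with the two-sided test in section 13 or with the increase stated in section 9, so they do not support the sentence.

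Third, a reader might infer that clustering takes power down to a known lower value, or that type II error runs as high as 16%. The documents do not support either. The SAP calls clustering a potential source and gives nothing from which to size it; the 16% needs an assumed design effect of about 1.10. Separate pregnancies of one mother may have been allocated to different arms, which would offset part of the loss. Only the direction, probably downward, can be taken from the plan.

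**Conclusion.** The sentence is wrong as written. At the SAP's own inputs, and assuming equal arms, power is about 87% (86 to 87% by the pooled, exact chi-square and log relative risk methods). Type II error before any clustering is about 13 to 14%, against the stated 10%. This rests on reading 15% as percentage points, which the relative risk of 1.33 confirms, and on the two-sided 5% test of section 13. It does not depend on the clustering argument.

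The shortfall is modest. It does not call for more participants or a different analysis, and it would be wrong to infer from it that the study is unfit for purpose. It matters because the figure will be used to interpret a null result on a primary outcome.

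**What to change.** Replace the power sentence for the composite in section 9 with wording such as:

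> With 420 participants (equal arms assumed), power to detect 45% v 60% (RR 1.33) is about 87% before any allowance for clustering; 90% power corresponds to about 45% v 60.7% (15.7 points, RR 1.35).

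If the actual split of the 420 is known without unblinding, it can replace the equal-arms assumption; the figure will hardly move.

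Add a sentence saying that within-mother clustering, as described in the first addendum, is likely to lower this power somewhat, with the sponsor's own cluster share and intraclass correlation and their source. The design effects used above are illustrations and should not be copied into the SAP. While editing, the sponsor should confirm that 45% still fits the composite now that gestational diabetes has been added.

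The cost is SAP wording only, and a slightly less favourable figure. Recruitment, data collection and the analysis do not change.

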### 10. Analysis based on Self-reported Outcomes

An aim of this research program is to compare outcomes based on expert clinical synthesis of administrative and self-reported data and those based on questionnaire responses completed by

each participant. A complementary analysis of the appropriate outcomes indicated in section 5 above by the superscript S (self-reported) will be completed with all participants for those questions which most closely match the outcomes listed in section 5.

## 11. Exploratory analyses

### 4.6. Enriched Sample Analysis

Where appropriate data from outcomes obtained at the 30-year follow up will be incorporated in the outcomes and the denominators corrected to include the number of participants in each treatment arm for whom data were available at either 30-year or 50-year follow up.

### 4.7. Subgroup analyses

Exploratory analyses for primary and secondary outcomes will investigate if the treatment effect of antenatal corticosteroid is influenced by the following variables:

- Trial protocol (standard-dose treatment compared with double-standard dose)
- Multiple pregnancy (singleton pregnancy compared with multiple pregnancy)
- Sex of the infant
- The tocolytic used (ethanol vs salbutamol vs none/unknown)
- The reason for preterm delivery

Analyses for each of the outcomes listed will be performed with each of these potential subgroups as main and interaction effects (with treatment allocation) and measures of effect will be presented for each of the subgroup strata.

### 4.8. Sensitivity analyses

The following sensitivity analyses will be performed to examine the primary and secondary outcomes:

- Excluding participants for whom there were protocol deviations (per protocol analysis)
- Including current BMI, sex, current socioeconomic status, gestation at birth and birthweight z score (1) in the adjusted analysis

In addition, the following sensitivity analyses will be performed for diabetes outcomes

- Excluding participants for whom the reason for preterm birth was listed as maternal diabetes mellitus
- Excluding participants for whom there was a known family history of diabetes mellitus noted at 30 year follow-up

For the secondary outcome *Hierarchical win ratio outcome* a sensitivity analysis will be performed using time to death after 28 days, excluding those with fetal death or death before 28 days from the analysis.

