#### 4.5. Covariates and potential confounders

Adjusted and unadjusted results will be presented for all outcomes. The results will be adjusted based on the following variables. Additional baseline variables will be included in the model if these differ markedly between treatment groups and are known to influence the particular outcome.

- Gestational age at randomisation (continuous variable)

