**Table 2 Baseline characteristics of participants whose mothers were randomised to betamethasone and placebo**

|                                                | Betamethasone | Placebo |
|------------------------------------------------|----------------------|----------------|
| Maternal Characteristics                |                      |                |
| Gestational age at entry, days (mean, SD)      |                      |                |
| Gestational age at delivery, days (mean, SD)   |                      |                |
| Multiple pregnancy (%)                         |                      |                |
| Singleton                                      |                      |                |
| Multiple                                       |                      |                |
| Unplanned premature labour (%)                 |                      |                |
| Planned delivery (%)                           |                      |                |
| Hypertension-oedema-proteinuria syndromes      |                      |                |
| Rh isoimmunisation                             |                      |                |
| Placenta praevia                               |                      |                |
| Diabetes mellitus                              |                      |                |
| Other                                          |                      |                |
| Mode of delivery (%)                           |                      |                |
| Normal vaginal delivery                        |                      |                |
| Instrumental delivery                          |                      |                |
| Caesarean section                              |                      |                |
| Tocolytic used (%)                             |                      |                |
| Ethanol                                        |                      |                |
| Salbutamol                                     |                      |                |
| Both                                           |                      |                |
| Treatment dose of betamethasone or placebo (%) |                      |                |
| Standard dose                                  |                      |                |
| Twice standard dose                            |                      |                |

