| Protocol deviations (%)                        |                      |                |
| Neonatal Characteristics                |                      |                |
| Female (%)                                     |                      |                |

|                                    |  |  |
|------------------------------------|--|--|
| Term delivery (%)                  |  |  |
| Birthweight, g (mean, SD)          |  |  |
| Birthweight Z score (mean, SD)     |  |  |
| 5 minute Apgar score <7 (%)        |  |  |
| Respiratory distress syndrome (%)  |  |  |
| Adult Characteristics       |  |  |
| Age at follow up, years (mean, SD) |  |  |
| Ethnicity (%)                      |  |  |
| Māori                              |  |  |
| New Zealand European               |  |  |
| Pacific                            |  |  |
| Other                              |  |  |
| Smoking status (%)                 |  |  |
| Non-smoker                         |  |  |
| Previously smoked                  |  |  |
| Currently smokes                   |  |  |

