| Overweight or obesity (n/N, %)                                                                                                                |  |  |  |  |  |
| BMI (continuous) (mean, SD)                                                                                                                   |  |  |  |  |  |
| Death from any cause (n/N, %)                                                                                                                 |  |  |  |  |  |
| Time to death after randomisation (mean, SD)                                                                                                  |  |  |  |  |  |
| Time in Hospital per 10 years alive after 1988 (mean, SD)                                                                                     |  |  |  |  |  |

|                                                                                                                                                                                                                                            |  |  |  |  |  |
|--------------------------------------------------------------------------------------------------------------------------------------------------------------------------------------------------------------------------------------------|--|--|--|--|--|
| Self-reported general health (mean, SD)                                                                                                                                                                                        |  |  |  |  |  |
| Rate of admissions to hospital with respiratory illness as the primary reason for admission/per patient year of followup (mean, SD)                                                                                            |  |  |  |  |  |
| Chronic respiratory illness (Self-reported diagnosis of asthma, self-reported chronic respiratory symptoms, admissions for asthma or chronic obstructive pulmonary disease [COPD] or prescription of pharmaceuticals for asthma or COPD) c |  |  |  |  |  |
| Asthma (n/N, %)                                                                                                                                                                                                                |  |  |  |  |  |

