| Type 2 diabetes mellitus                                                                                         |  |  |  |  |  |
| Type 1 diabetes mellitus                                                                                         |  |  |  |  |  |
| Gestational diabetes mellitus                                                                                    |  |  |  |  |  |
| Excluding participants for whom there was a known family history of diabetes mellitus noted at 30 year follow-up |  |  |  |  |  |
| Diabetes mellitus (any type)                                                                                     |  |  |  |  |  |
| Type 2 diabetes mellitus                                                                                         |  |  |  |  |  |
| Type 1 diabetes mellitus                                                                                         |  |  |  |  |  |
| Gestational diabetes mellitus                                                                                    |  |  |  |  |  |

Relative risk, Hazard ratio, Mean difference, Adjusted for current BMI, sex, current socioeconomic status, gestation at birth and birthweight z score in the adjusted analysis

Table 9 Sensitivity analysis for win-odds hierarchical outcome analysis excluding those with fetal death or death before 28 days

| Outcome | Betamethasone
N = | Placebo
N = | Odds Ratio
(95% CI) | P value |
|---------|----------------------|----------------|------------------------|---------|
|---------|----------------------|----------------|------------------------|---------|

|                                              |  |  |  |  |
|----------------------------------------------|--|--|--|--|
| Win-odds
Hierarchical
outcome |  |  |  |  |
|----------------------------------------------|--|--|--|--|

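### The section 4.8 sensitivity model adjusts every primary and secondary outcome, BMI included, for variables arising after randomisation, and section 4.5 does not define which baseline variables may enter the main model

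*SAP*

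**What the plan says.** **Main adjusted model (SAP section 8, subsection 4.5).** Adjusted and unadjusted results are both to be shown for every outcome. One covariate is fixed by name: gestational age at randomisation, as a continuous variable. A rule then opens the list: "Additional baseline variables will be included in the model if these differ markedly between treatment groups and are known to influence the particular outcome". Baseline is not defined, and no candidate variables or threshold are given.

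**Sensitivity model (SAP section 11, subsection 4.8).** The list opens with "The following sensitivity analyses will be performed to examine the primary and secondary outcomes", and one of its items is "Including current BMI, sex, current socioeconomic status, gestation at birth and birthweight z score (1) in the adjusted analysis". The Table 8 footnote repeats the set: "Adjusted for current BMI, sex, current socioeconomic status, gestation at birth and birthweight z score in the adjusted analysis". Neither place exempts any outcome. The first addendum adds another item to this list and leaves this one unchanged.

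**Outcomes (SAP section 5.2 and Table 4).** Continuous BMI (mean difference) and overweight or obesity (relative risk) are both secondary outcomes.

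**What the SAP calls baseline (Tables 1 and 2).** Table 2 is headed "Baseline characteristics of participants whose mothers were randomised to betamethasone and placebo". It includes gestation at delivery, mode of delivery, birthweight, Apgar score, "Respiratory distress syndrome" and adult smoking status. Table 1 has the same birth and neonatal rows.

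**The concern.** The stated aim is to learn whether antenatal corticosteroids have long-term effects on offspring, analysed by the mother's allocation. That is a total effect of allocation. Current BMI, current socioeconomic status, gestation at birth and birthweight z score all come after randomisation, so treatment could in principle change any of them.

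Three things follow:

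- Where the outcome is BMI, or a category of BMI, the model cannot estimate a treatment effect at all.
- For other outcomes, conditioning on a variable that treatment affects changes the question. The study hypothesis is that there is no long-term adverse impact. If a harm ran through one of these variables, the model would tend to remove it, and under a sensitivity label the null result could be read as confirmation.
- The rule in 4.5 reaches the main adjusted model. An undefined baseline, in a document whose baseline tables contain post-randomisation rows, leaves room for the same problem there.

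**Working it through.** The plan gives no figure for this point, so there is none to reproduce. The passages can be set against each other, and the consequences follow from algebra and small simulations.

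**1. Timing of each covariate**

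| Covariate | Where | Fixed before treatment? |
|---|---|---|
| Gestational age at randomisation | 4.5, main model | Yes |
| Sex | 4.8 only (also a subgroup factor) | Yes |
| Gestation at birth | 4.8 | No |
| Birthweight z score | 4.8 | No |
| Current BMI | 4.8 | No |
| Current socioeconomic status | 4.8 | No |

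**2. BMI as the outcome.** The model is BMI = a + b × treatment + c × BMI. The exact least-squares solution is a = 0, b = 0, c = 1, whatever the data. In a simulated sample of 420 with a treatment difference of 1.75 (SE 0.50) in the unadjusted fit, adding BMI as a covariate gave a treatment coefficient of about 1.6 × 10⁻¹⁵ and R-squared of 1.

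**3. Overweight or obesity as the outcome.** Assume it is defined by a cut-off on the same BMI; 25 was used here, and any cut-off behaves alike. In the simulated sample the highest BMI without the outcome was 24.99 and the lowest with it was 25.07, so BMI separates the outcome completely. A logistic fit failed with a singular matrix. A log-binomial fit, the SAP's model for binary outcomes, reported convergence with a treatment coefficient of −0.0162 (SE 0.0016). That ratio is about −10, and its sign is opposite to the simulated BMI difference. The estimate has no meaning.

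**4. Other outcomes.** All effect sizes here are assumptions.

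- Treatment raises BMI by d units, each BMI unit adds 0.03 to the log risk, and there is no direct effect.
- Total RR = exp(0.03d). For d = 0, 1, 2 this is 1.00, 1.03, 1.06.
- RR adjusted for BMI is 1.00 in all three cases, so the mediated effect is removed.
- Now add an unmeasured cause U that raises BMI by 2.4 units per SD and log risk by 0.1 per SD. The other variation in BMI has SD 4.
- Given treatment, the slope of U on BMI is 2.4 / (2.4² + 4²) = 2.4 / 21.76 = 0.110.
- The adjusted treatment coefficient is −0.1 × 0.110 × d = −0.011d, so the adjusted RR is 1.00, 0.99, 0.98. The total RR is unchanged.

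| d (BMI units) | Total RR | Adjusted, no U | Adjusted, with U |
|---|---|---|---|
| 0 | 1.00 | 1.00 | 1.00 |
| 1 | 1.03 | 1.00 | 0.99 |
| 2 | 1.06 | 1.00 | 0.98 |

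The first row matters: if treatment does not affect the covariate, there is no bias.

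**5. The 4.5 rule against Tables 1 and 2.** The rule admits baseline variables. The only tables the SAP titles as baseline contain gestation and mode of delivery, birthweight, Apgar score and respiratory distress syndrome. SAP section 3 gives the last of these as what the original trial sought to improve. The rule does not point to the tables, but nothing in it excludes these rows.

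**The case against.** The strongest reply is structural. The four post-randomisation covariates appear only in a sensitivity analysis under exploratory analyses. The fixed main covariate precedes treatment, unadjusted results are always shown, and Table 8 names the added covariates. All of this stands. A reader might infer that the plan's primary estimates are biased by the 4.8 set; the documents do not support that.

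A reader might also infer that the plan will adjust for respiratory distress syndrome. No section says so: 4.5 does not cite Table 2, and Table 2 separates neonatal and adult rows under their own sub-headings (although gestation and mode of delivery sit under the maternal heading). Such adjustment is permitted, not planned. The SAP gives no rates of respiratory distress syndrome by arm, so no size is offered for it.

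Leaving sex out of the main model may look like an error. Treatment does not affect sex, so omitting it does not bias a randomised comparison. It costs precision.

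The shifts in the example are also modest. Assuming 210 per arm (half of the SAP's 420) and 45% with the outcome in each arm, SE(log RR) = √(2 × 0.55 / (0.45 × 210)) = 0.108. The 95% interval then spans factors of about 0.81 to 1.24, wider than the 6% to 8% shift at d = 2. The concern is therefore what the analysis means rather than a large numerical distortion.

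Finally, one can say that BMI on BMI would be noticed at once. That is true for continuous BMI. It is less sure for overweight or obesity, where the log-binomial fit above returned a plausible-looking estimate with a small standard error.

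**Conclusion.** The point holds within limits.

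- **Certain from the text:** as written, the 4.8 model puts BMI on both sides for continuous BMI. For overweight or obesity it gives complete separation, provided the outcome is a cut-off on the same BMI.
- **Conditional:** for other outcomes the model does not test the robustness of the total effect of allocation if treatment affects one of the four covariates. Under the assumptions above, a total RR of 1.03 to 1.06 becomes 1.00, or 0.98 to 0.99 with an unmeasured shared cause. With no treatment effect on the covariate, nothing is lost.
- **Open wording:** 4.5 leaves the main adjusted model unfixed and does not confine additions to variables measured before randomisation.

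The fixed main model and the unadjusted results are not compromised by the 4.8 set.

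**What to change.** **Section 4.5.** Limit covariates to variables fixed before treatment. Delete the imbalance rule, or confine it to variables measured before randomisation. Prespecify infant sex alongside gestational age at randomisation, for precision and not as a correction of bias.

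**Section 4.8 and the Table 8 footnote.** Drop current BMI, current socioeconomic status, gestation at birth and birthweight z score. Alternatively, keep them only as a labelled exploratory mediation-type analysis that excludes BMI and overweight or obesity. If kept, state that unmeasured causes shared by these variables and the outcome can bias the estimate; relabelling alone does not make it a valid direct effect.

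**Cost.** SAP wording, and one covariate that the plan already uses elsewhere. No new data are needed.
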